## Abstract

**Background:**

Non-invasive brain stimulation (NIBS) techniques are now widely used in patients with disorders of consciousness (DOC) for accelerating their recovery of consciousness, especially minimally conscious state (MCS). However, the effectiveness of single NIBS techniques for consciousness rehabilitation needs further improvement. In this regard, we propose to enhance from bottom to top the thalamic–cortical connection by using transcutaneous auricular vagus nerve stimulation (taVNS) and increase from top to bottom cortical-cortical connections using simultaneous high-definition transcranial direct current stimulation (HD-tDCS) to reproduce the network of consciousness.

**Methods/design:**

The study will investigate the effect and safety of simultaneous joint stimulation (SJS) of taVNS and HD-tDCS for the recovery of consciousness. We will enroll 84 MCS patients and randomize them into two groups: a single stimulation group (taVNS and HD-tDCS) and a combined stimulation group (SJS and sham stimulation). All patients will undergo a 4-week treatment. The primary outcome will be assessed using the coma recovery scale-revised (CRS-R) at four time points to quantify the effect of treatment: before treatment (T0), after 1 week of treatment (T1), after 2 weeks of treatment (T2), and after 4 weeks of treatment (T3). At the same time, nociception coma scale-revised (NCS-R) and adverse effects (AEs) will be collected to verify the safety of the treatment. The secondary outcome will involve an analysis of electroencephalogram (EEG) microstates to assess the response mechanisms of dynamic brain networks to SJS. Additionally, CRS-R and AEs will continue to be obtained for a 3-month follow-up (T4) after the end of the treatment.

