### Sample size

The sample size was calculated based on the effective rate. An improvement of at least 3 points in the CRS-R was considered an effective treatment. Previous studies found the effective rate of taVNS was 7% (*n* = 14) (7) and of HD-tDCS was 36% (*n* = 11) (21). Assuming the existence of a synergistic effect, the SJS group will have a higher effective rate of 43%, while the sham stimulation group will have no effect. Therefore, the two-sided 2 × 4 chi-square test in PASS (version 15) was used for the sample size calculation of four groups. The test power (1-β) was 80% and the type I error rate (α) was 5%. The calculated effect size W was 0.436, and then a dropout rate of 20% was considered. Finally, a total of 84 patients will eventually be enrolled, and each group will have 21 patients (Figure 2).

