### Statistical analysis

IBM SPSS Statistics 26 software will be used for statistical analysis. The measurement data will be tested for normal distribution by using Kolmogorov-Smirnov tests. Data conforming to a normal distribution will be analyzed by ANOVA or repeated measures ANOVA for differences in each treatment group. Data not conforming to a normal distribution will be analyzed by the Kruskal-Wallis H test or Friedman test. *Post hoc* tests will be carried out with Bonferroni. Count data will be expressed as cases or percentages, and differences between groups for count data with all theoretical frequencies greater than 5 will be tested by the chi-square test, otherwise, Fisher’s exact test will be used. *p* < 0.05 will be considered to indicate statistically significant differences.

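### The aim of verifying the safety of combined stimulation goes beyond what a p < 0.05 difference test with 21 patients per arm can support

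*Protocol article*

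**What the plan says.** The abstract (Methods/design) makes safety an aim beside efficacy and says how it will be met: "nociception coma scale-revised (NCS-R) and adverse effects (AEs) will be collected to verify the safety of the treatment". The end of the Introduction and the end of the Discussion repeat the joint aim of efficacy and safety.

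The Statistical analysis section is the only place that states between-group inference. Measurement data go to ANOVA or Kruskal-Wallis, or their repeated-measures counterparts. Count data are first summarised as cases or percentages, and then "differences between groups for count data with all theoretical frequencies greater than 5 will be tested by the chi-square test, otherwise, Fisher’s exact test" is used. Post hoc "tests will be carried out with Bonferroni", and p "< 0.05 will be considered to indicate statistically significant differences". The section names neither adverse effects nor NCS-R, but the first are counts and the second is a score, so both fall under its general rules.

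The Sample size section rests on the proportion of patients gaining at least 3 CRS-R points and concludes that "a total of 84 patients will eventually be enrolled, and each group will have 21 patients", after allowing for 20% dropout.

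Other safety provisions stand elsewhere:
- Table 1 lists withdrawal for recurrent seizures and life-threatening disease.
- Procedures gives reports to the Ethics Committee after every 10 patients, with assessment of causality, and termination for a serious event proven to be caused by treatment.
- Stimulations and Behavioral assessments use NCS-R to adjust the taVNS current.

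**The concern.** The stated aim and the stated method do not fit together. A difference test can show harm. It cannot show safety, because failing to reject equality is also the expected result when the arms differ and the sample is small. The article offers no other route from group data to a statement about the safety of SJS.

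This matters more than usual here, for three reasons in the article itself. Procedures shortens the taVNS session because of the current intensity of the combined treatment. The Discussion notes that these patients cannot report symptoms, so detection of adverse effects is already insensitive. And NCS-R steers the taVNS current during stimulation, so any between-arm NCS-R comparison is pulled toward no difference by design. At stake is a report that finds no significant difference in adverse effects and presents that as verified safety, while the data still allow a large excess on SJS.

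**Working it through.** **Inputs from the article.** Four arms, 21 patients each (Sample size). Dropout of 20%, so 21 × 0.8 = 16.8, about 17 per arm. Two-sided 5% level; Fisher's exact test where an expected count is not above 5 (Statistical analysis).

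**The plan's own figure.** The article states no power, rate, margin or precision for safety, so there is no safety figure to reproduce. Its only size figure is for efficacy. With W = 0.436, 3 degrees of freedom, 5% level and 80% power, the noncentral chi-square gives N = 58, and 58 / 0.8 = 72.5, so 73 rather than 84. That mismatch concerns efficacy and is not used here.

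**Assumed inputs.** Adverse-effect rates on SJS and sham are not given, so a range is shown.

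**Step 1: how often Fisher's test misses an excess.** For n per arm and true rates p₁ and p₂:

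miss = Σₓ Σᵧ Bin(x; n, p₁) · Bin(y; n, p₂), summed over all tables (x, y) with two-sided Fisher p ≥ 0.05.

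| Assumed rates, SJS v sham | Miss, n = 21 | Miss, n = 17 |
|---|---|---|
| 20% v 10% | 92% | 95% |
| 20% v 5% | 82% | 88% |
| 30% v 10% | 74% | 81% |
| 25% v 5% | 68% | 78% |
| 40% v 10% | 48% | 61% |
| 50% v 10% | 24% | 37% |
| 30% v 0% | 20% | 39% |

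If the Bonferroni correction is applied over all six pairs (level 0.05 / 6), 25% v 5% is missed 95% of the time at either size, and 40% v 10% is missed 79% (n = 21) or 83% (n = 17).

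**Step 2: what a clean result excludes, with no assumed rate.** With zero events of a type in n patients, the exact two-sided 95% upper limit is 1 − 0.025^(1/n).
- n = 21: 1 − 0.025^(1/21) = 0.161, or 16%.
- n = 17: 1 − 0.025^(1/17) = 0.195, or 20%.

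**Step 3: one concrete table.** Take 5/21 on SJS and 1/21 on sham. The difference is 23.8% − 4.8% = 19.0 points, and Fisher's p = 0.18. The Newcombe 95% interval runs from about −3 to +41 points. The test reports no significant difference; the interval shows that an excess of up to 41 points has not been excluded.

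**Step 4: NCS-R, if the arms are compared.** Two-sample t test, 0.5 SD difference, noncentrality 0.5 × √(n/2). The miss rate is 65% at n = 21 and 71% at n = 17. For 0.8 SD it is 28% and 38%. These figures take no account of the current adjustment, which would shrink the observable difference further.

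**The case against.** A reader might infer that the p < 0.05 test is the trial's only safety rule. It is not. Table 1, Procedures, Stimulations and Behavioral assessments all contain safety rules. They act on individual patients, or stop the trial for a proven treatment-caused serious event. They do not say when group data would show SJS to be safe, so they narrow the point without removing it.

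A reader might also infer that the protocol will treat non-significance as proof of safety. No sentence says so. The strong verb appears once, in the abstract; elsewhere the article speaks of investigating or looking into safety. What stands is that the article promises verification and states only a method that cannot deliver it.

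It can fairly be said that the miss rates depend on the chosen scenarios. They do, and the table shows very large excesses being found in most trials. The 17-per-arm column may also be pessimistic, because some dropouts will themselves be adverse-effect cases (recurrent seizures are a reason for withdrawal) and would still be counted.

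Two further objections hold. NCS-R is described operationally as a guide for current and for judging pain, and no between-arm comparison of it is named, so step 4 is conditional. And sizing on efficacy alone, or leaving a safety margin to a fuller plan, is ordinary practice and is no fault in itself. The Statistical analysis section also already promises counts and percentages, so part of the reporting is in place.

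**Conclusion.** The point holds as a mismatch between a stated claim and a stated method. With 21 patients per arm, the difference test would miss a moderate excess of adverse effects on SJS in roughly half to nine-tenths of trials (48% for 40% v 10%, 92% for 20% v 10%). That range rests on assumed rates and on comparing two arms by Fisher's test. It does not extend to excesses such as 50% v 10%, missed 24% of the time. The 16% upper limit after zero events in 21 patients needs no assumed rate and is enough to show that the trial can describe safety but not verify it. The documents do not support the stronger readings, that there is no other safety rule or that a false safety rule has been written down. The change is worth making because it alters what the trial may conclude about safety.

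**What to change.** In the abstract, change *verify* to *describe*. In Statistical analysis, add a short paragraph on safety:

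- For any adverse effect and for each type, give the number of patients affected per arm with an exact 95% confidence interval (including the upper limit when no event occurs), and the SJS-minus-sham risk difference with its 95% interval.
- Report any between-arm NCS-R comparison as a difference with its 95% interval, and note that NCS-R was also used to adjust the taVNS current.
- State that no safety conclusion rests on a non-significant test.

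A pass mark for acceptable safety based on a margin is not recommended. The documents give no basis for its value, and at an assumed 10% rate (one-sided 0.025, 80% power) a 15-point margin would need 63 patients per group and a 10-point margin 142.

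The cost is a few sentences, with no new patients or data. The downside is a weaker safety claim, with intervals that will be wide at this size.

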**Discussion:**

This study protocol aims to innovatively develop a full-time and multi-brain region combined neuromodulation paradigm based on the mesocircuit model to steadily promote consciousness recovery by restoring thalamocortical and cortical-cortical interconnections.

## Introduction

Disorder of consciousness (DOC) is caused mostly by disruption of thalamocortical and cortical-cortical connections due to extensive destruction of long-range white matter fiber tracts after severe brain injury (1). Typically, patients with DOC are classified into two levels of consciousness according to CRS-R: vegetative state/unresponsive wakefulness syndrome (VS/UWS), comprising those who retain only basic brainstem reflexes and sleep-wake cycles but no purposeful behavior, and minimally conscious state (MCS), comprising those who have fluctuating but reproducible signs of consciousness such as movement to command, visual pursuit, and localization to noxious stimulation (2).

In recent years, neuromodulation techniques have played an important role in treating neurological disorders through interventions on key hubs of the brain networks. taVNS is a novel NIBS technique that is safe and easy to use at home. It has been widely used and confirmed to have a good clinical effect on psychiatric disorders such as depression, insomnia, and cognitive disorders (3). In 2017, our team initially applied taVNS to patients with DOC and reported a case of a VS/UWS patient who improved to MCS after treatment (4). Briand et al. (5) further proposed a vagal cortical pathway model and suggested that taVNS might enhance the afferent signals from the auricular branch of the vagal nerve, promoting activity of the tractus solitarius nucleus and spinal trigeminal nucleus. Then, the neural impulses along the ascending reticular activating system (ARAS) strengthened from bottom to top the thalamic-striatal-cortical interaction to promote the recovery of consciousness (Figure 1) (5). Similarly, a subsequent longitudinal case study found another patient had improved from VS/UWS to MCS during taVNS treatment. However, the patient never fully regained consciousness after 6 months of continuous treatment and even had a downward trend in CRS-R after the end of treatment (6). Another study with a larger sample size reported that only 5 out of 14 DOC patients showed improvement in consciousness after treatment with taVNS (7). Similar results reported by Yu et al. (8) showed also that only 50% of patients with DOC had a good outcome after treatment. The fluctuation in the effective rate between study groups demonstrated that taVNS had a poor and unstable therapeutic effect on patients with DOC, which suggested a limited understanding of the underlying mechanism of taVNS for consciousness. That highlighted the urgent need for additional in-depth studies.

**Figure 1 fig1:**
[figure not shown]
Mechanism of action of simultaneous taVNS and HD-tDCS. taVNS, transcutaneous auricular vagus nerve stimulation; HD-tDCS, high-definition transcranial direct current stimulation; 5-HT, 5-hydroxytryptamine pathway; NE, norepinephrine; ARAS, ascending reticular activating system.

Yu et al. (8) further discovered a significant increase in cerebral blood flow in DOC patients with better prognoses after 1 month of taVNS treatment. The affected regions included the right thalamus, right caudate nucleus, left insula, superior temporal gyrus, left prefrontal cortex, precentral gyrus, and left occipital cortex. An EEG study also found that frontal–parietal and frontal-occipital connectivities were enhanced in MCS patients after 2 weeks of taVNS treatment (9). For the healthy subjects, a review pointed out that taVNS might commonly activate the thalamus, striatum, medial prefrontal cortex, and postcentral gyrus via the 5-hydroxytryptamine pathway of raphe nucleus and the norepinephrine pathway of locus coeruleus (5). In addition, studies using EEG have found increased power in lower frequency bands in healthy subjects after stimulation of taVNS, especially in the frontal and central regions (10). Based on the above evidence, we hypothesize that taVNS may initially activate the frontal regions at the cortical-cortical level. Then, these signals will disseminate to the parietal and occipital lobes through anatomical connections. However, the indirect weak effects via frontal cortex connectivity may not be enough to completely activate the posterior brain regions (Figure 1). According to the global workspace hypothesis, the formation and maintenance of consciousness required the integration of information from a large-scale frontoparietal network (11). Schiff et al. also proposed the mesocircuit model. They suggested that the initiation of consciousness relied on the interconnection via the thalamus between the frontoparietal network and anterior forebrain mesocircuit, which includes the frontal and prefrontal cortex and the striatopallidal negative feedback loop (1, 12). In conclusion, taVNS may modulate only a single neural circuit or local brain area, which cannot trigger the reconstruction of a complete consciousness network.

Transcranial direct current stimulation (tDCS) is another NIBS technique and is characterized by direct modulation of cortico-cortical connections in a top-down manner (13). Conventional tDCS consists of two electrode pads. The anode increases the excitability of the target area through subthreshold weak stimulation, while the cathode acts as an inhibitor (14). It is generally accepted that the selection of stimulation sites is a critical factor influencing the moderator effect of tDCS on neural networks (15–17). The precuneus and posterior cingulate cortex (PCC) are key nodes of the default mode network (DMN) in the posterior brain region. The precuneus/PCC and the posterior medial cortex were recognized as regions with the highest metabolic activity during the resting state in healthy subjects (18). In addition, the functional diversity and integration of the precuneus and PCC were significantly lower in patients with DOC than in healthy subjects (19). Another study further revealed that an increase in the metabolic ratio of the precuneus to the central thalamus was accompanied by improved levels of consciousness (20). Therefore, the activity of precuneus and PCC was correlated with the level of consciousness. Consequently, it was expected to be a potential stimulation site of tDCS in posterior brain regions to promote restoration of consciousness. A randomized, crossover, controlled trial found that nine patients with DOC showed behavioral recovery after repeated treatments of tDCS targeting the posterior parietal cortex (PPC) for 5 days. But the overall effective rate of the tDCS montages targeting the PPC was lower than the tDCS targeting the dorsolateral prefrontal (15). This disparity in effectiveness might be attributed to the diffuse current of tDCS that could not precisely and effectively stimulate the PPC. In this regard, HD-tDCS with a more focused stimulation current was developed to induce focal neural and specific behavioral changes. Guo et al. (21) used HD-tDCS targeting precuneus to treat patients with DOC and established that 72% (9/11) of patients with DOC had a significant increase in CRS-R scores. Furthermore, the simultaneous EEG results indicated a significant change in central-parietal connectivity, suggesting that HD-tDCS activated a wide range of brain activity outside the target (21). Thus, it seemed that HD-tDCS had a clear modulatory effect on the posterior brain regions of patients with DOC. But the overall effective rate of HD-tDCS for consciousness recovery was still precarious due to different stimulation paradigms in various studies (21–23).

In summary, we propose to enhance from bottom to top the overall activity of the anterior forebrain mesocircuit by using taVNS. Furthermore, HD-tDCS targeting precuneus will be used at the same time to compensatively enhance the frontoparietal network to overcome the issue that single NIBS techniques were insufficient to activate the large-scale consciousness circuit (Figure 1). Ultimately, the thalamocortical and frontoparietal network simultaneously will be maintained at a high level of excitability to restore the integrity of the consciousness network and accelerate the recovery of consciousness in patients with DOC. In the study, we will look into the clinical efficacy and safety of whole-time and multi-brain combined modulation to break the bottleneck of the unstable effect of NIBS techniques and deepen the understanding of the mechanisms of consciousness onset and maintenance in DOC patients.

## Methods

### Study design

The study is a prospective, randomized, controlled, double-blind clinical trial (Figure 2) that has been registered at the Chinese Clinical Trial Registry (ChiCTR2300069166). The study protocol is designed according to the Declaration of Helsinki and has been approved by the Ethics Committee of Beijing Tiantan Hospital, Capital Medical University (NO. KYSQ 2022-347-01). Informed consent will be obtained from a patient-authorized legal representative due to patients’ disorders of consciousness.

**Figure 2 fig2:**
[figure not shown]
Study flow diagram. taVNS, transcutaneous auricular vagus nerve stimulation; HD-tDCS, high-definition transcranial direct current stimulation; NCS-R, nociception coma scale-revised; EEG, Electroencephalogram; CRS-R, coma recovery scale-revised.

### Participants

The study has initiated in April 2023 and will continue until December 2024. A total of 84 MCS patients will be included in the Neurosurgery Inpatient Department of Beijing Tiantan Hospital. The inclusion and exclusion criteria are presented in Table 1.

**Table 1 tab1:** Inclusion and exclusion criteria.

**Inclusion**	
	1. Diagnosed with MCS by coma recovery scale-revised;
	2. Age: from 18 to 60 years;
	3. More than 1 month after the initial brain injury;
	4. Consciousness is in a stable phase (no change in the total score of CRS-R) for at least 2 weeks before admission;
	5. No cranial defect or extensive skull repair;
	6. Precuneus and posterior parietal should be intact on at least one side;
	7. Patient-authorized legal representative agreed to the experimental protocol and signed informed consent.
**Exclusion**	
	1. Neurodegenerative diseases such as Alzheimer’s disease and Lewy body dementia; 2. Disorders of consciousness caused by operation injuries or malignancy;
	3. Time since onset less than 1 month (acute coma);
	4. Patients with seizures that are difficult to control;
	5. Patients are undergoing other clinical trials;
	6. Pregnancy and lactation.
**Withdrawal**	
	1. Recurrent seizures during treatment;
	2. Life-threatening diseases such as severe lung infection, intracranial infections, and cerebral hernia;
	3. Death;
	4. Patient is lost to follow-up.

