### Procedures

The randperm function of MATLAB (Version 2020b, MathWorks Inc., Natick, United States) will be used to generate 84 random integers in random order by the study leader. Each patient will be given a random number in the order of enrollment. The first randomization will divide patients into a combined stimulation group (1–42) and a single stimulation group (43–84) based on a 1:1 ratio. Patients in the combined stimulation group will be further randomized in a 1:1 ratio into the SJS group (1–21) and the sham stimulation group (22–42). Similarly, patients in the single stimulation group will also be randomly assigned in a 1:1 ratio to the taVNS group (43–63) and the HD-t DCS group (64–84).

The study protocol is a double-blind design. Each patient will be exposed to identical-looking simultaneous stimulation. Specifically, the SJS group will receive both positive stimulation of taVNS and HD-tDCS. In contrast, the sham stimulation group will receive sham stimulation of taVNS and HD-tDCS to eliminate potential brain effects caused by the physical compression of the instrument. The patients in the single stimulation group will receive one kind of positive stimulation by taVNS or HD-tDCS. They will also receive sham stimulation of another technique at the same time to blind patients/families and therapists/assessors.

All patients will receive treatment twice a day in the morning and afternoon for 4 weeks. There are 2 days’ rest every 5 days of treatment. Considering the high current intensity of SJS, the single stimulation time of taVNS, commonly for 30 min (24), will be adjusted downward to 20 min to reduce the burden on the patient’s brain.

The Ethics Committee of Beijing Tiantan Hospital will be responsible for independent security monitoring. Adverse events and unintended events will be reported to them when every 10 patients are included. They will further assess the causal relationship between the adverse reaction and treatment. If a serious adverse event is proven to have been caused by the treatment, the trial will be terminated immediately. Appropriate medical emergency and protective measures will be given to patients at the same time.

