### Stimulations

The stimulation area of the taVNS (SDZ-IIB, Suzhou Medical Supplies Factory) will be bilateral auricles. A pair of clips will be placed on one side of the auricle and another pair of clips will be placed on the opposite side. A clip will have three carbon-impregnated silicone tips. The first tip will serve as the common end of the other two tips to support the posterior surface of the auricle. The second tip will be placed on the lateral scapha. The third tip will be placed on the medial auricular cavity to stimulate targets including cymba conchae and cavum conchae (Figure 1). The stimulator will provide electrical pulses of 1–1.5 mA with an alternate frequency between 4 and 20 Hz and a pulse width of 30 μs. Stimulus intensity will be routinely set at 1.5 mA for each patient. We will turn down the current when the patient’s blood oxygen saturation is below 95%, heart rate increases by more than 20%, or the NCS-R score exceeds 3 points and shows a significant increase during stimulation compared to pre-stimulation. The stimulator will have no ramp-up and ramp-off of current during the stimulation. In addition, two identical-looking instruments will be used. One, called number 1, will be capable of normal stimulation as positive stimulation after the switching on. However, the other one, called number 2, will have no current output as a sham stimulation.

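### Table 1 treats recurrent seizures and life-threatening illness as withdrawal, with no route to stop stimulation and stay in the study, so later CRS-R and adverse-effect data may be lost for reasons tied to outcome

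*Protocol article*

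**What the plan says.** The Withdrawal block of Table 1 has four items. The first is "Recurrent seizures during treatment" and the second is "Life-threatening diseases such as severe lung infection, intracranial infections, and cerebral hernia". The third and fourth are death and loss to follow-up. The block does not say what the patient is withdrawn from.

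Other places that bear on the point:

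- **Abstract, Methods/design.** The aim covers both benefit and harm: "The study will investigate the effect and safety of simultaneous joint stimulation (SJS) of taVNS and HD-tDCS for the recovery of consciousness". CRS-R at T0 to T3 is the primary outcome. On later data the abstract says: "Additionally, CRS-R and AEs will continue to be obtained for a 3-month follow-up (T4) after the end of the treatment".
- **Table 1, Exclusion.** "Patients with seizures that are difficult to control" are not enrolled.
- **Stimulations.** The only step described for an individual patient is to lower the taVNS current, when "blood oxygen saturation is below 95%, heart rate increases by more than 20%, or the NCS-R score exceeds 3 points" (the last with a significant rise from before stimulation).
- **Procedures.** Adverse events go to the Ethics Committee after every 10 patients. "They will further assess the causal relationship between the adverse reaction and treatment". A serious event proven to be caused by treatment stops the whole trial.
- **Follow-up period.** Every patient is to be followed for 3 months from the end of treatment, with CRS-R and adverse effects recorded every 2 weeks in the first month and monthly after that. Remote, home and proxy assessments are allowed. Withdrawn patients are not mentioned.
- **Sample size.** "The calculated effect size W was 0.436, and then a dropout rate of 20% was considered".

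**The concern.** Death and loss to follow-up end data collection by their nature. Seizures and severe illness do not: they are reasons to stop stimulating, and the patient can usually still be assessed. Putting all four under one heading gives them the same status, and the protocol offers no intermediate step.

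Two things are at stake.

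- **Efficacy.** Recurrent seizures, intracranial infection and cerebral hernia can change CRS-R, so the missing scores would be missing for reasons tied to the primary outcome.
- **Safety.** Hard-to-control seizures are excluded at entry, so seizures that recur under stimulation are events whose later course the safety question needs. Whether they settle once stimulation stops also informs the Ethics Committee's judgement on causality.

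Data not collected at the time cannot be recovered by any later analysis.

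**Working it through.** **1. The text side by side.** Table 1 states a withdrawal rule with no stay-in-study option. Stimulations offers only a lower taVNS current; Procedures offers only termination of the whole trial. The Follow-up period section speaks of every patient, but it cannot literally cover everyone on the Withdrawal list, because that list includes the dead and the lost. It also starts at the end of treatment. Even on its most generous reading it therefore secures nothing at T1, T2 or T3 for a patient stopped early. The result is an ambiguity whose natural reading loses data.

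**2. What one withdrawn patient could miss.** Scheduled post-baseline assessments: T1, T2 and T3 (3), plus follow-up contacts of 2 in month one, 1 in month two and 1 in month three (4, the last being T4). Total 3 + 4 = 7. Withdrawal before T1, T2 or T3 could lose 7, 6 or 5 of the 7.

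**3. Illustration on the response rate (assumed counts).** The documents give no rate for these events. Assume k = 1 to 4 patients per arm of 21. The upper end takes all of the planned 20% dropout as coming from the first two items: 0.20 × 21 = 4.2. If k outcomes are unknown and r responders are seen among the rest, the rate over all randomised lies between r/21 and (r + k)/21, a width of k/21.

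| k | width, one arm (points) |
|---|---|
| 1 | 4.8 |
| 2 | 9.5 |
| 3 | 14.3 |
| 4 | 19.0 |

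For a difference between two arms the widths add. With four lost in each, (4 + 4)/21 = 38.1 points.

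For scale, the planned gaps from SJS (Sample size) are 43 − 36 = 7 points against HD-tDCS, 43 − 7 = 36 against taVNS and 43 − 0 = 43 against sham. A gap is a between-arm difference, so the two-arm width is the right comparison when both arms lose patients. In the most extreme assumed case, 38 points covers the first two gaps but not the third.

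**4. Power.** For the planned 2 × 4 chi-square test, df = 3, α = 0.05, noncentrality λ = N × 0.436² = N × 0.1901.

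- N = 84: λ = 15.97, power 0.934.
- N = 67 (84 × 0.8 = 67.2): λ = 12.74, power 0.863.
- Smallest N with at least 80% power: 58 (λ = 11.03, power 0.805).

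The stated total of 84 is not reproduced: 58/0.8 rounds up to 73. The stated total is the larger, so the mismatch is on the safe side, and it is a separate matter. Even with the full planned dropout, power stays above 80%.

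**The case against.** The strongest reply is that the point rests on a one-word heading. Table 1 does not say that assessment stops, the wording of the first item also fits stopping treatment, and the only text on who is followed names every patient without exception. The document is an article, and a fuller protocol could spell out what happens after stimulation stops. Analysis populations belong to an analysis plan that is not shown.

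Part of this stands. The heading is ambiguous and the sections do not contradict each other. The absence of a stated analysis set is not faulted here. What does not stand is the claim that nothing was fixed badly. The article states a rule, places two stimulation-stopping events in it beside two unavoidable exits, and gives no sentence that keeps the first two under assessment. The follow-up text does not repair this for T1 to T3.

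A reader might infer more than the documents support:

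- **That seizures would go unreported.** They would not. The event is reported and assessed for causality under Procedures; what may be lost is its later course and delayed effects.
- **That the rule biases the trial in favour of SJS.** No document shows that losses would differ by arm. One can construct a case: if four non-responders left SJS, 9/21 = 43% would read as 9/17 = 53%. That assumes losses in one arm only, all of them non-responders, and a complete-case analysis that the Statistical analysis section does not specify.
- **That only the 7-point gap could be blurred.** That holds only if losses fall in one arm; with four lost in each of two arms the 36-point gap is within the range too.
- **That power is at risk.** Step 4 shows it is not.

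**Conclusion.** The concern holds as a poorly drawn withdrawal rule that should be reworded. In its natural reading, patients with recurrent seizures or life-threatening illness leave the study, and CRS-R and adverse-effect data are then missing for reasons related to outcome, in a trial that sets out to study safety as well as effect.

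The size cannot be derived, because no event rate is given. The ranges of 4.8 to 19.0 points for one arm and up to 38 points for a two-arm difference rest on an assumed one to four losses per arm. They describe how uncertain the rates would be, not a bias that has been shown. Confidence is moderate, because the heading can be read more kindly.

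**What to change.** In Table 1, move the first two Withdrawal items to a separate list of reasons to stop stimulation. Limit study exit to death, withdrawn consent and true loss to follow-up.

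In the Follow-up period section, add that a patient whose stimulation is stopped keeps CRS-R and adverse-effect assessments on the original calendar: T1 to T3 as scheduled, the interim follow-up contacts, and T4 at 3 months after the planned week 4. Use the remote, home or proxy routes already allowed where a visit is not possible. State that these patients are analysed in the arm to which they were randomised.

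The cost is a change of protocol wording and a few extra contacts with sicker patients. Some legal representatives may decline further assessment, so some data will still be missing, but for a recorded reason.
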